#### Qualitative data collection (step II)

Qualitative data will be collected from a number of sources: semi-directed interviews with key informants (patients, professionals, managers) (*n* = 12 per case) [68], document analysis (tools used in care coordination and continuity, chart review, meeting minutes) [69] and observation (follow-up appointments, team meetings). Tracer patients, referring to patients followed throughout the healthcare process [70, 71], will enable documentation of transitions in real time (interviews, observation, clinical chart). The selection of tracer patients (*n* = 16) will be based on cancer type (breast, colorectal, prostate) and affiliation with a family physician in a FMG involved in one the two cases of the study. Patients over 70 years of age will make up 50% of tracer cases given their increased potential for multimorbidity [72], the recognition of unmet needs in this group [73] and the challenges of an integrated oncogeriatric approach [67]. Professionals involved in the care of these tracer patients will be interviewed to incorporate views on the context and mechanisms (active ingredients) of real-world care transitions from people directly involved in the RbCCCM.

#### Qualitative data analysis (step II)

Systematic and iterative content analysis will involve listening to the audio of interviews, reading and coding all data [54] integrated into a QDA Miner database. A semi-open analytical grid, based on the analytical framework (Fig. 1) will enable an initial coding structure and the addition of new codes during analysis [74]. Each case will be analyzed separately, followed by an inter-case analysis to highlight recurring models, differences and similarities between the cases (semi-regularities) [43].

#### Validity (step II)

Validity is increased through the triangulation of multiple data sources [54] and the interactions between researchers and potential knowledge users. Collaborative coding based on solid theory and concepts, along with validation of findings by users will contribute to internal validity (credibility). The detailed description of the RbCCCM and cases will contribute to external validity (transferability) and the pragmatic aims of the study.

#### Step III - Outcomes of the RbCCCM

This stage aims to understand the outcomes of the RbCCCM in patients and professionals in each of our cases. It uses experimental approaches to verify our working hypothesis that the RbCCCM will have a positive impact on professional practice and the care experience of cancer survivors (patient-reported experience). The impossibility, for ethical and professional reasons, of conducting a randomized controlled trial calls for a pragmatic before-and-after design with delayed intervention (6-month follow-up) where teams in one case will provide usual care (control segment) while teams in the other case are implementing the components of the intervention (intervention segment). This step will answer Question 3.

#### Sample (step III)

The sample size is calculated according to our previous studies on the responsiveness of cancer care [75] and the Health Education Impact Questionnaire (heiQ) scoring for self-management capacity [76]. Given that scores on the scales range between 1 and 4, an average score of 2.3 and a difference of 0.3 are reasonable. One hundred patients per case will be recruited, based on anticipated attrition of about 10%. If we consider the heiQ distress score, this sample size would enable us to detect a 0.3 difference between measures at 2 time points in a same group, and between groups, with a standard deviation of 0.71 and confidence interval of 0.80.

The sample size will include about 50 professionals per case (100 total) including personnel in the FMGs and the cancer care teams. The minimum response rate based on our previous studies is anticipated at 40%. Limitations related to the small sample size will, as is common in case studies, be compensated by the qualitative data described in Step II [77].

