### Demonstration project

The design for analyzing the implementation (Step II) and evaluation of outcomes (Step III) is a multiple case study [54] based on qualitative and quantitative data [55]. The design is appropriate to understanding a contemporary phenomenon (the RbCCCM) as it manifests in the real world where it may be influenced by multiple changing and interdependent factors and contextual challenges. A case is defined as the cancer care trajectory in order to understand how the RbCCCM mobilizes members of specialized cancer care teams and primary care teams during transitions.

The selection of cases is based on theory [54] to represent real-world differences [56] in terms of geographic location (the territorial expanse served; rural/semi-urban/urban areas), mission (academic or not), the size and diversity of care teams and their interest in being involved in the RbCCCM demonstration project. Units of analysis are the hospital-based cancer care teams and the FMGs of two Integrated Health and Social Service Centres (3/11 FMGs + one hospital in Saguenay-Lac-Saint-Jean (Case 1); 3/31 FMGs + one hospital in the Montérégie (Case 2). The selection of cases is also influenced by feasibility and our knowledge of these establishments gained through their participation in prior research we conducted on cancer care [8, 37, 38, 57–63], on primary care [64, 65], as well as on organizational factors that influence the care experience of people having received a cancer diagnosis [38].

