#### Quantitative data analysis (step III)

Descriptive statistical analyses, comparative analyses based on data type (t-test, Chi2, ANOVA, ANCOVA), and regression analyses (multilevel logistic and linear because of the structure and hierarchy of data) will be conducted. These will enable us to determine the association (positive, negative or neutral) between the RbCCCM, professional practice, and the care experience of cancer survivors during transitions, while controlling for certain potentially confounding individual and organizational variables. The threshold for significance will be 5%.

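### The sample-size statement labels power as a confidence interval, and its 0.80 for the between-case comparison assumes independent patients although the plan calls the data hierarchical

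*Protocol article*

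**What the plan says.** The Sample (step III) section of the protocol article sets the patient number: "One hundred patients per case will be recruited, based on anticipated attrition of about 10"%. For the heiQ distress score it then claims that this number suffices to find a change of 0.3 from T0 to T1 within a case and a gap of the same size from one case to the other. The inputs to that claim are worded: "with a standard deviation of 0.71 and confidence interval of 0.80". Power is not named, and the section gives no ICC, design effect or T0-T1 correlation.

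Three other sections bear on this statement:

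- Quantitative data analysis (step III) lists t-test, Chi2, ANOVA and ANCOVA together with "regression analyses (multilevel logistic and linear because of the structure and hierarchy of data"). It also fixes the test level: "The threshold for significance will be 5"%.
- Demonstration project places three FMGs and one hospital in each of the two cases and says: "Units of analysis are the hospital-based cancer care teams and the FMGs".
- Step III - Outcomes of the RbCCCM describes a non-randomised before-and-after design with delayed intervention, in which "teams in one case will provide usual care (control segment) while teams in the other case are implementing the components of the intervention".

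**The concern.** There are two problems. First, a confidence interval is not a single number such as 0.80. If the phrase means 80% confidence, it conflicts with the 5% threshold in the analysis section. A reader has to guess that power is meant.

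Second, the number fits a calculation that treats patients as independent, while the analysis section says that they are not. Patients who share an FMG share clinicians and local practice, and the intervention is delivered to whole teams. Any positive correlation within FMGs widens the standard error of the between-case difference, and the sample size contains no allowance for it.

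What is at stake is how the between-case result for Question 3 will be read. A null result from a study believed to have 80% power could be taken as evidence of no effect, when the power of the announced analysis may be much lower. The Validity (step III) section also rests internal validity partly on sample size.

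**Working it through.** **Inputs from the article.** Difference 0.3; SD 0.71; 100 recruited per case; attrition 10%, so 90 completers per case; significance 5%; three FMGs per case.

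**Assumptions, not in the article.** Two-sided test; equal recruitment, so 90/3 = 30 completers per FMG; ICC 0.01 to 0.05; T0-T1 correlation r = 0.5 for baseline adjustment.

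**Step 1: reproduce the stated figure, with 0.80 as power.**
- n per case = 2 × [(1.960 + 0.842) × 0.71 / 0.3]² = 87.9, so 88.
- After attrition: 88 / 0.9 = 97.8, so 98. The article states 100.
- Power at 90 per case: SE = 0.71 × √(2/90) = 0.1058 and 0.3/SE = 2.834. This gives 80.9% by normal approximation and 80.5% by the exact t-test.
- A one-sided test would need only 70 per case, which does not fit. With 0.80 read as 80% confidence (alpha 0.20), power at 90 per case would be 94%, which does not explain the sample size either.

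So 0.80 is two-sided 5% power for independent patients. The allowance of 100 against 98 leaves almost nothing over.

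**Step 2: between-case power with FMG clustering, T1 scores unadjusted.** Design effect DE = 1 + (30 − 1) × ICC; SE = 0.71 × √(2 × DE/90). Power is Φ(0.3/SE − 1.96), or comes from a noncentral t with 6 − 2 = 4 df. The detectable difference at 80% power is 2.802 × SE, or 3.761 × SE on 4 df.

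| ICC | DE | SE | Power (normal) | Power (4 df) | Detectable (normal) | Detectable (4 df) |
|---|---|---|---|---|---|---|
| 0 | 1.00 | 0.106 | 81% | 57% | 0.30 | 0.40 |
| 0.01 | 1.29 | 0.120 | 70% | 48% | 0.34 | 0.45 |
| 0.02 | 1.58 | 0.133 | 62% | 41% | 0.37 | 0.50 |
| 0.05 | 2.45 | 0.166 | 44% | 29% | 0.46 | 0.62 |

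By the normal approximation, power falls below 80% once the ICC exceeds about 0.0008.

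**Step 3: the same with adjustment for T0 (ANCOVA).** The SE is multiplied by √(1 − r²) = √0.75 = 0.866.

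| ICC | Power (normal) | Power (4 df) |
|---|---|---|
| 0 | 91% | 69% |
| 0.01 | 82% | 59% |
| 0.02 | 74% | 51% |
| 0.05 | 55% | 36% |

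**Step 4: within-case change, 90 pairs, independent patients.** SD of change = 0.71 × √(2(1 − r)). Power by normal approximation is 81% at r = 0 (80% by the exact paired t-test), 92% at r = 0.3 and 98% at r = 0.5. If 0.71 is already the SD of change, power is 98%.

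**The case against.** The arithmetic itself is right. With the label corrected, 100 per case follows from the stated inputs, so this is a wrong label and an unstated assumption, not a miscalculation. That stands.

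A reader might infer that 100 patients per case simply fail to give 0.80. The article does not support that. It gives no ICC, it measures outcomes at T0 and T1, and it lists ANCOVA. With r = 0.5 and a large-sample reference, 80% is kept up to an ICC of about 0.013, and with r = 0.6 up to about 0.021. The shortfall is therefore conditional. It appears at larger ICCs, and at r = 0.5 it appears at every ICC once the test uses 4 df. The sample-size statement also names no T0-T1 correlation, so it cannot be taken as already claiming this gain.

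A reader might also infer that the within-case claim is overstated. It is not: for independent patients 0.80 is a floor at any non-negative correlation.

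A third tempting inference is that the listed t-tests will produce inflated false-positive rates. That would follow only if they carried the inference, and the article already plans multilevel regression.

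Finally, the phrase about units of analysis is case-study language and does not make FMGs the statistical unit. The clustering argument rests on the declared hierarchy and the three FMGs per case, and the figure of 30 per FMG is an assumption. This is also a demonstration project with a large qualitative component, which limits the weight placed on power but does not make the sentence correct.

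**Conclusion.** The statement is wrong as written in one respect and incomplete in another. The label is wrong without any assumption: 0.80 is power, and reading it as confidence conflicts with the 5% level. For the between-case comparison, 0.80 holds only if patients are independent, which contradicts the article's own reason for multilevel models, or if an unstated gain from baseline adjustment makes up the loss.

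The size of the shortfall depends on an ICC that the article does not give. Over assumed ICCs of 0.01 to 0.05, unadjusted power ranges from about 70% down to 44%, or 48% down to 29% on 4 df. T0 adjustment at a correlation of 0.5 raises this to 82% down to 55%, or 59% down to 36% on 4 df. The label and the independence assumption are certain; the loss of between-case power is conditional. The within-case claim needs no correction on these grounds.

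**What to change.** - In Sample (step III), replace the words "confidence interval of 0.80" with a statement of power 0.80 at two-sided 5%, assuming independent patients.
- Restate between-case power, or the detectable difference, as a range over assumed ICC and T0-T1 correlation, including the 4-df figures. Unadjusted, the detectable difference is about 0.34 to 0.46, or 0.45 to 0.62 on 4 df, for ICC 0.01 to 0.05.
- In Quantitative data analysis (step III), base between-case inference on the multilevel model already planned, adjusted for the T0 score and with a small-sample reference suited to six FMGs. Keep the unadjusted t-test, Chi2 and ANOVA as descriptive.

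No extra patients are needed. The cost is a less favourable stated power and a narrower role for the simple tests, which is a small change to the analysis as well as to the wording. None of this separates region from intervention. With one region per arm, the between-case contrast carries any regional difference at any sample size, and the restated text should say so.

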#### Procedure (step III)

The patient recruitment process is based on our previous studies. It relies on collaboration from care teams to help us identify potential patient participants. Standardised criteria and recruitment procedures will be used and a local professional (the research nurse in our study) will be designated to explain the study and obtain informed consent. If the patient agrees to participate, they will be given a postage-paid envelope, information letter and printed questionnaire. Patients may also choose to complete the questionnaire on line (SurveyMonkey Inc., San Mateo, California, USA). In this case, patient participants will be given an access code. Questionnaires are anonymous and managed to respect confidentiality. Reminders and a compensation of $25 aim to increase response rates.

All professionals working in specialized cancer care and primary care teams will receive an invitation by email that includes a link to a short video explaining the study objectives and expectations of participants. The questionnaire will be provided in print and on line (SurveyMonkey Inc., San Mateo, California, USA). Three reminders at two-week intervals, along with marketing through communities of practice, scientific networks (e.g. RRISIQ, Réseau 1, CANO) and social media, along with compensation of $25, aim to increase response rates [78].

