#### Quantitative data collection (step III)

Anticipated outcomes in patients will be measured before the intervention (T0) and six months after the start of the RbCCCM (T1). A self-administered questionnaire (30 min) will measure the patient’s perception of their experience of care during transitions between teams: responsiveness [75]: timeliness of access (4 items; α = 0.77), person-centred care (5 items, α = 0.67), quality of communication (5 items, α = 0.85), self-management capacity based on the heiQ validated in oncology [76], involving: emotional distress (6 items; α = 0.77), wayfinding in the health system (5 items, α = 0.85), social support and integration (5 items, α = 0.85), as well as quality of life SF12 (12 items, α = 0.83) [79]. Though the project does not include an economic evaluation, data related to some costs will be collected, notably among men with prostate cancer [80], using a generic instrument and a diary to report costs of using health care (time, transport costs, non-reimbursed medication costs, lost income). This data will provide the basis for economic analysis in a future study. Sociodemographic and clinical data will be collected: age, gender, comorbidity, cancer type, health status, chronic diseases [81], survivorship profile [82].

Anticipated outcomes among professionals will be measures before the intervention (T0) and 6 months after the start of the RbCCCM (T1), an interval based on feasibility in a demonstration project. A self-administered questionnaire (30 min) with validated psychometric properties will be employed: SCOP scope of practice (26 items, α = 0.89) [83], teamwork (5 items, α = 0.84) [84], team environment (19 items, α = 0.88–0.93) [85], shared leadership (13 items, α = 0.66) [86]. The density and centrality of intra- and inter-team links will be measures using social network analysis [87]. Data on sociodemographic characteristics will also be collected (age, gender, profession, practice setting, years of experience).

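### Patient questionnaires are declared anonymous, which conflicts with following the same patients from T0 to T1; read literally, paper forms could not be paired

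*Protocol article*

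**What the plan says.** All references are to the protocol article, Step III.

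- **Procedure (step III), patients.** A research nurse obtains informed consent. Consenting patients receive a printed questionnaire with a prepaid return envelope, or may answer online. For the online option: "In this case, patient participants will be given an access code". No identifier is described for the printed form. The paragraph then states: "Questionnaires are anonymous and managed to respect confidentiality". It ends: "Reminders and a compensation of $25 aim to increase response rates".
- **Step III – Outcomes of the RbCCCM.** The design is before-and-after with delayed intervention and 6-month follow-up. One case gives usual care while the other implements the model.
- **Sample (step III).** One hundred patients per case are recruited, with about 10% attrition expected. The claim is that "this sample size would enable us to detect a 0.3 difference between measures at 2 time points in a same group, and between groups", with SD 0.71.
- **Quantitative data collection (step III).** Patients are measured before the intervention (T0) and six months after its start (T1).
- **Quantitative data analysis (step III).** The methods are t-test, chi-square, ANOVA, ANCOVA and multilevel regression, with a 5% significance threshold. No paired test is named, and the T0 score is not named as the ANCOVA covariate.

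**The concern.** The design, the attrition allowance and the comparison of two time points in one group all describe a cohort seen twice. A cohort analysis needs each T1 form matched to its T0 form. Anonymity, in its ordinary sense, removes that match. The sentence names anonymity alongside confidentiality, so it is not obvious that it loosely means coded. The one code that is described belongs to the online route.

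If the forms went out without a code, the data would be two unlinked cross-sections per case. Nobody could compute a patient's change, adjust for that patient's T0 score, or compare those who dropped out with those who stayed.

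This matters most for the difference in change between cases. The two cases were chosen to differ in location, mission and prior initiatives, and this contrast removes a constant difference between them. The problem also cannot be repaired afterwards: once uncoded T0 forms have been returned, the link is gone.

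**Working it through.** **Inputs.** From Sample (step III): difference 0.3, SD 0.71, 100 per case, 10% attrition, hence 90 evaluable per case. The 0.80 that this section calls a confidence interval is read as power. From the analysis section: 5% significance, taken as two-sided because the article does not say. The T0–T1 correlation ρ is not given, so a range of 0.2 to 0.7 is assumed. All figures use the normal approximation and treat patients as independent.

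**1. The stated sample size.** For two independent means:

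n = 2 × (1.96 + 0.842)² × 0.71² / 0.3² ≈ 88 per group; 88 / 0.90 ≈ 98.

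This agrees with the stated 100. At 90 per group, SE = 0.71 × √(2/90) = 0.106 and power = Φ(0.3/0.106 − 1.96) ≈ 81%. The stated number is therefore the independent-samples calculation and uses no T0–T1 correlation.

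**2. T0 against T1 within one case.** Treated as independent samples with 90 at each time, nominal power is the same 81%. Paired, SE = 0.71 × √(2(1 − ρ)/90). At ρ = 0.5 this is 0.0748 and power is 98%. If the same patients answer twice but cannot be paired, the unpaired test is conservative. Its true power at ρ = 0.5 is Φ((0.3 − 1.96 × 0.1058)/0.0748) ≈ 89%. The loss in this contrast is modest.

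**3. Difference in change between the cases.**

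- Unlinked: SE = 0.71 × √(4/90) = 0.150; power = Φ(0.3/0.1497 − 1.96) = Φ(0.044) ≈ 52%.
- Linked: SE = 0.71 × √(2(1 − ρ)) × √(2/90) = 0.1497 × √(1 − ρ).

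| ρ (assumed) | Linked power | Unlinked power | Loss (points) |
|---|---|---|---|
| 0.2 | 61% | 52% | 9 |
| 0.3 | 67% | 52% | 15 |
| 0.4 | 74% | 52% | 22 |
| 0.5 | 81% | 52% | 29 |
| 0.6 | 89% | 52% | 37 |
| 0.7 | 95% | 52% | 44 |

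The 52% hardly moves if the same people answer twice without being paired: true power is then 52% to 53% over this range. The test is conservative, and without pairs ρ cannot be estimated to correct the standard error.

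**4. Adjustment for the T0 score.** With residual SD 0.71 × √(1 − ρ²), a linked ANCOVA at 90 per case has power of about 83%, 84%, 90% and 98% at ρ = 0.2, 0.3, 0.5 and 0.7. These figures suppose cases with similar T0 means.

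**The case against.** The strongest reply is that the article never says T0 and T1 will be unlinked. Consent through a research nurse, an access code, reminders, compensation and an attrition allowance all suggest that individuals are tracked. *Anonymous* may be a loose word for coded, and a condensed article may leave the coding scheme to the full protocol. Silence about a code on paper forms is not a rule against one. All of this stands, and it limits how serious the point is. It does not remove the conflict, because anonymity is stated and is not merely left undetailed.

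Three stronger readings are tempting and are not supported:

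- **That the planned analyses are blocked.** Repeated cross-sections can still be compared, and ANCOVA or regression on other covariates still runs. The analysis section names neither a paired test nor T0 as a covariate. Multilevel models need a Family Medicine Group (FMG) label, which an anonymous form can carry. Return counts at each time show overall attrition, and reminders can go to every enrolled patient.
- **That power falls below what was planned.** The two stated contrasts keep about 80% nominal power without linkage, since the sample size assumed none. No power is stated for the difference in change. Linkage alone would not secure 80% there either: at ρ = 0.3 it gives 67%.
- **That the loss is about 30 points.** This is the result at ρ = 0.5 only, and the article gives no ρ.

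**Conclusion.** The point holds as a conflict in the stated text. The procedure declares patient questionnaires anonymous and describes a code only for online responders, while the rest of Step III follows the same patients from T0 to T1. If the sentence is followed literally, paired tests, change scores and T0-adjusted ANCOVA are lost for paper forms.

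The 9 to 44 point loss for the difference in change is conditional. It rests on a literal reading of anonymity applied to all forms, on the assumed range of ρ, on a two-sided 5% test with 90 evaluable per case, and on ignoring clustering. With two cases and three FMGs in each, the absolute power figures are optimistic. The comparison of linked with unlinked data is more useful than either figure alone.

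The sentence should be reconciled with the design before T0 forms go out. A reader might infer that the trial cannot link its data at all; the article does not establish that. If a coding scheme already exists, this is a wording error and no power is lost.

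**What to change.** - In Procedure (step III), replace the claim of anonymity by a statement that questionnaires are confidential and coded.
- Give each patient one study code. Use it as the online access code and print it on the paper form, at both T0 and T1. The research team holds the key.
- Record the case and FMG with the code.
- State that change analyses use the linked data with adjustment for the T0 score.

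The cost is a change to consent and ethics wording and printing a code on the forms. Some patients may answer slightly less candidly on a coded form. If the full protocol already specifies such a code, only the sentence in the article needs correcting.
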